### Methods to protect against sources of bias

#### Randomization and allocation

The randomization process is not predictable, thereby reducing any potential for experimenter bias to influence participants’ allocation. The randomization scheme will be created by a random number-generating website (https://www.randomizer.org). The randomization sequence generation will take place prior to the recruitment of participants and will be completed by a Healthy HEARTS’ staff member not associated with the study, resulting in a completely random assignment of groups to the two conditions without investigator interference. Opaque envelopes will contain the randomization result for all groups. The envelopes are kept in a locked file cabinet to which assessors and research assistants do not have access.

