**Methods:**

A randomized controlled trial (RCT) design with repeated measures will be used to evaluate the effectiveness of MBCT to treat psychological distress in pregnancy. A sample of 60 consenting pregnant women aged 18 years and above will be enrolled and randomized to the experimental (MBCT) or control (treatment as usual) condition. Primary (e.g., symptoms of stress, depression, and anxiety), secondary (cortisol, blood pressure (BP), heart rate variability (HRV), and sleep) and other outcome data (e.g., psychological diagnoses) will be collected via a combination of laboratory visits and at-home assessments from both groups at baseline (T_1_), immediately following the intervention (T_2_), and at 3 months postpartum (T_3_). Descriptive statistics will be used to describe sample characteristics. Data will be analyzed using an intention-to-treat approach. Hierarchical linear models will be used to test intervention effects on primary and secondary outcomes.

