## Methods

### Study design

The study is a two-arm, single-blinded, parallel-group RCT with equal allocation of participants and a repeated measure design. Table 1 illustrates the overall study design and process of enrollment, allocation, and follow-up of participants in the trial. The trial is being conducted at the Healthy HEARTS Laboratory, University of Calgary, Alberta, Canada. Ethics approval has been obtained from the University of Calgary, Conjoint Health Research Ethics Board (CHREB). Any trial amendments will be approved by CHREB before implementation and will be reported to the trail registry. A copy of the Standard Protocol Items: Recommendations for Interventional Trials (SPIRIT) checklist can be seen in Additional file 1.

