### Baseline assessment

If no exclusionary criteria are met, participants will complete a battery of questionnaires assessing a host of demographic (e.g., age, gestational age, marital status, ethnicity, education, household income) and psychosocial (e.g., depressive and anxiety symptoms, positive and negative affect, worry, rumination, life satisfaction, and mindfulness) constructs. After questionnaires are completed, physiological measures will be obtained, including assessments of BP, heart rate variability (HRV), and a stress reactivity task. On the two weekdays immediately following the initial visit, participants’ salivary cortisol will be self-collected via oral swabs and an objective assessment of sleep quality will be obtained via actigraphy. All assessments occur within 2 weeks of participants being randomized to either an MBCT or a control group. All baseline measures will be collected before randomization occurs. A detailed description of all measures is presented below.

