#### Both groups

All participants who come to the laboratory will complete baseline (T_1_) measures prior to randomization. After enough participants have completed baseline assessments to form an adequately large MBCT group they will be randomly assigned using a block randomization procedure. Once all participants know their group assignment, they will be informed of their program start date by a study coordinator who is not involved in assessments. After randomization occurs, strategies will be employed to ensure that the assessors of outcomes remain blind to the experimental condition of all participants. All participants are invited back to the laboratory post treatment (T_2_) and at 3 months postpartum (T_3_) to complete the same measures. Data about any services received for management of mental health problems outside the study will be collected at each study assessment visit.

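### The allocation section has groups assigned to conditions, while the rest of the protocol randomizes individual women; the unit of randomization must be reconciled

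*Protocol article*

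**What the plan says.** The protocol article describes the unit of assignment in two ways.

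**The individual woman.** The Abstract (Methods) says "A sample of 60 consenting pregnant women aged 18 years and above will be enrolled and randomized". Study design calls the trial a "parallel-group RCT with equal allocation of participants and a repeated measure design". Baseline assessment says "All assessments occur within 2 weeks of participants being randomized to either an MBCT or a control group". Both groups gives the procedure: "After enough participants have completed baseline assessments to form an adequately large MBCT group they will be randomly assigned using a block randomization procedure". Statistical analyses places every participant in the arm to which she was randomized. Randomization and allocation opens in the same sense ("The randomization process is not predictable, thereby reducing any potential for experimenter bias to influence"), a sentence that goes on to speak of the allocation of participants.

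**The group.** Later in Randomization and allocation, the sequence is described as "resulting in a completely random assignment of groups to the two conditions without investigator interference", followed by "Opaque envelopes will contain the randomization result for all groups".

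The Sample size section counts women (21 per arm, 26 after attrition). Statistical analyses describes a hierarchical linear model for repeated measures and names no level for cohort or recruitment wave.

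**The concern.** Randomization and allocation is the only section on how the sequence is generated and concealed, so it is where staff or a reader would look to learn what is randomized. Its wording has groups as the things assigned and the two conditions as what they are assigned to. Both groups adds that women accumulate until there are enough for an MBCT group and are assigned only then. Call each such set of women a wave. The text then admits two procedures: women split 1:1 within a wave, or a wave sent whole to MBCT or to usual care.

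The two differ in what the data can support. If waves were assigned whole, arm would be confounded with whatever varies between waves, such as season, recruitment source or gestational mix. The independent units would be a handful of waves and not 60 women, and an individual-level p-value would overstate the evidence. This is separate from the nesting of MBCT women in therapy classes, which arises even when women are randomized individually.

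**Working it through.** **1. The passages side by side**

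| Section | Unit implied |
|---|---|
| Abstract, Methods | woman (60 enrolled and randomized; blocks not mentioned) |
| Study design | woman (equal allocation of participants) |
| Baseline assessment | woman |
| Both groups | woman, in blocks, once enough have finished baseline |
| Statistical analyses | woman |
| Randomization and allocation, opening | woman |
| Randomization and allocation, sequence | group |
| Randomization and allocation, envelopes | group (number of results per group or per woman not stated) |

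If the groups were the two arms, the sequence sentence would say that arms are assigned to themselves, and speaking of all groups would be odd for two arms. The groups could instead be the allocation lists for each wave, which would fit individual randomization. The text does not say which.

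**2. Which unit the plan's own figures assume**

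Inputs from Sample size: d = 0.5, two-sided 0.05, 21 per group, 95% power. A plain two-sample comparison does not reproduce this: it needs 104 per arm for 95% power, and 21 per arm gives about 35% (t test). A repeated-measures group-by-time F test with f = d/2 = 0.25, three time points and an assumed correlation of 0.5 gives 94.6% at N = 42. That correlation and that test are not stated in the section, and whether 21 is adequate is a separate question. What matters here is that every version counts women as independent units and has no design effect. The figures therefore fit individual randomization only.

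**3. What would follow if waves were assigned whole (illustration)**

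Neither the number of waves G nor the intracluster correlation (ICC) is in the document. Assumed: 60 women, G = 6, 8 or 10, ICC = 0.01, 0.05 or 0.10.

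- Wave size: m = 60/G, so 10, 7.5 or 6.
- Design effect: DE = 1 + (m − 1) × ICC.
- Approximate true type I error of an individual-level test with critical value 2.00 (t, 58 df): 2 × P(Z > 2.00/√DE).

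| G | m | DE at ICC 0.01 / 0.05 / 0.10 | Type I error |
|---|---|---|---|
| 6 | 10 | 1.09 / 1.45 / 1.90 | 5.5% / 9.7% / 14.7% |
| 8 | 7.5 | 1.065 / 1.325 / 1.65 | 5.3% / 8.2% / 11.9% |
| 10 | 6 | 1.05 / 1.25 / 1.50 | 5.1% / 7.4% / 10.2% |

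Worked corner: G = 6, ICC = 0.10 gives DE = 1 + 9 × 0.10 = 1.90; 2.00/√1.90 = 1.451; 2 × P(Z > 1.451) = 14.7%.

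**4. If women are randomized individually**

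The design effect from assigning whole waves does not arise, and correcting the text changes no figure in the plan.

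**The case against.** The best reply is that this is loose wording. Five other sections and the opening of the allocation section itself make the woman the unit. The word cluster never appears, no section says that intact cohorts are allocated, and the sample size and model are at the level of the woman. That is good evidence of intent, and it stands: individual randomization is the likelier reading.

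A reader might go further than the text allows in three ways.

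- **That the trial is cluster-randomized and its power and analysis are therefore invalid.** The document does not establish this. The illustration applies only under the less likely reading and rests on assumed wave numbers and correlations; at its low end the error rate is essentially nominal.
- **That each group has a single envelope result.** The text gives no count per group or per woman.
- **That allocation is therefore discoverable.** This depends on the previous inference. It is also partly answered: all baseline measures precede randomization, a staff member outside the study generates the sequence, and the envelopes are locked away from assessors and research assistants.

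It is also fair to say that envelope numbering, and who opens the envelopes and when, are details an article leaves to the full protocol. They are not part of this point.

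The reply does not remove the contradiction. The article does not omit the unit; it states it in two incompatible ways, and the divergent statement sits in the section that governs allocation.

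**Conclusion.** The point holds as an internal contradiction about the unit of randomization, with a serious consequence only if the group wording is what was done. On the likelier reading the numerical effect is nil and the gain is a plan that says what was randomized. On the literal reading, treatment would be confounded with wave, and the individual-level sample size and a model without a wave level would not fit the design. A nominal 5% test would then run at about 5% to 15%, assuming 60 women, 6 to 10 waves and an ICC of 0.01 to 0.10. The article reports that recruitment is under way, so the procedure can still be confirmed and recorded.

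**What to change.** In Randomization and allocation, replace the two phrases about groups with a statement that the individual woman is the unit, allocated 1:1 in blocks within each wave that has completed baseline, and that there is one allocation result per woman. This brings the section into line with Both groups.

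Include wave, as the randomization stratum, in the outcome models. As a fixed effect this costs G − 1 degrees of freedom, that is 5 to 9 for the 6 to 10 waves assumed above.

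If any wave has already been assigned whole, disclose it and analyse it with the wave as the unit of assignment; the sample size would then also need restating for that design. Otherwise the cost is two sentences and one model term, with no change to the sample size.

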#### Blinding

Because participants are not blind to group allocation, before each follow-up visit the study research coordinator will call to remind participants that the research assistants conducting the clinical interview and administering the physiological measures are unaware of group assignment, and should remain so. In order to further minimize the chance of unblinding, the research coordinator will remind the participants about blinding a second time when they arrive for their follow-up visits, and the research assistant conducting the diagnostic interview will also do so at the outset of that interview.

#### Simultaneous interventions

The intervention was designed to be an adjunct to TAU care for pregnant women experiencing psychological distress in pregnancy. As such, information about any engagement in adjunctive therapies will be collected at each follow-up point (T_2,3_) to control for this variable in subsequent analyses if it is found to impact primary or secondary outcomes.

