#### Control condition

Participants in the TAU group are encouraged to engage in regular obstetrical and mental health care provided to them as part of their routine clinical care. All participants in the trial also receive an information pamphlet that contains contact numbers and website links for perinatal support services offered in Alberta. Participants are briefed with the information included in the pamphlet and informed about the perinatal support contacts should they choose to pursue treatment options.

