### Statistical analyses

Baseline characteristics (demographic and psychological) will be compared between groups using *t* tests (means) for continuous variables and chi-squared tests (%) for categorical variables to ensure randomization success. Any covariates found to differ significantly between groups will be held constant in between-group analyses. A significance level of .05 will be used for tests of all research hypotheses. The outcomes are between-group differences from baseline (T_1_) to post-intervention points (T_2,3_) on psychological and physiological measures. Analyses will be completed using Hierarchical Linear Modeling (HLM). HLM is a flexible approach to analysis of repeated measures data. For example, unlike analysis of variance (ANOVA), linear mixed models do not require that each participant has complete data to be included in the analysis, thus increasing their statistical power [104, 105]. All analyses will be completed using an intention-to-treat (ITT) approach—all participants will be included in the final statistical analysis according to the group (MBCT or TAU) to which they were randomized. To assess the effects of baseline psychological distress on outcomes, separate hierarchical mixed models of each outcome will be conducted using pretreatment psychological distress as a potential moderator.

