Limitations of this study include the use of a TAU control group, whereby women enrolled on the trial are free to pursue services for the treatment of psychological distress experienced in pregnancy. It is also possible that women randomized to either group may seek out pharmacological and/or psychological interventions for the treatment of psychological distress and this may limit our ability to detect group differences between MBCT and the control condition. However, the decision to use a TAU control group was made due to ethical considerations, as we did not wish to discourage pregnant women from seeking treatment while experiencing active distress. In order to control for other treatment potentially sought by participants, we are collecting data about alternative types of treatment that women pursued while in the study. An additional limitation is that the group recruited will be a heterogeneous sample that will have varying levels of psychological distress and diagnostic profiles. While this methodological decision was made to enhance external validity, it may reduce internal validity. In spite of its limitations, this project is one of few aimed at assessing both the potential psychological and physiological changes associated with evidence-based mindfulness interventions delivered in pregnancy. The current study design also has a number of strengths, including: (1) interviewer-assessed clinical diagnosis of psychological disorders, (2) longitudinal study design with follow-up that extends into the postpartum period, and (3) extensive physiological testing, including assessment of BP, HRV, stress reactivity, HPA function, and sleep.

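### The rule to control for other therapy taken up after randomisation is not confined to a supplementary analysis, and it can move the MBCT-plus-usual-care versus usual-care estimate in either direction

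*Protocol article*

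**What the plan says.** Under Simultaneous interventions, the article says that information on other therapies is collected at T2 and T3 "to control for this variable in subsequent analyses if it is found to impact primary or secondary outcomes". The limitations paragraph of the Discussion gives the same reason for collecting these data: "In order to control for other treatment potentially sought by participants". Neither place limits the adjustment to a sensitivity or supplementary analysis.

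Four other statements bear on it:

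- Baseline assessment: "All baseline measures will be collected before randomization occurs". Therapy recorded at T2 and T3 is therefore a post-randomisation variable.
- Simultaneous interventions: "The intervention was designed to be an adjunct to TAU care for pregnant women experiencing psychological distress in pregnancy".
- Control condition: women in the usual-care (TAU) arm are "encouraged to engage in regular obstetrical and mental health care provided to them as part of their routine clinical care".
- Statistical analyses: "All analyses will be completed using an intention-to-treat (ITT) approach", explained there as including everyone in the arm to which they were randomised. The covariate rule in that section concerns baseline characteristics that differ between arms. It does not mention other therapy.

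**The concern.** The trial asks what MBCT adds to usual care, and usual care includes whatever mental health treatment the women obtain. The Discussion expects women in both arms to seek drug or psychological treatment for distress, which is what MBCT is meant to reduce. Women on antidepressants or anxiolytics at entry are excluded, so any such drug use found at follow-up began after screening. Uptake can thus be a consequence of the arm and of how distressed a woman still is.

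Two things follow if uptake enters the model as a covariate. The arm coefficient becomes a contrast at a fixed level of other therapy, which is not the hypothesised comparison. It also loses the protection of randomisation, because women with the same recorded uptake in the two arms need not be alike in severity.

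The trigger adds a second problem. No criterion for impact is given, the check needs outcome data, and it could come out differently for each of the four primary scales (PRA, EDS, GAD-7, PSS-10) and for the physiological measures. At stake is whether the reported effect is the one the trial was set up to estimate, and whether the model was fixed before the data were seen.

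**Working it through.** The plan states no figure on this point, so there is none to reproduce. The check has a textual and a numerical part.

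**Text.** Baseline precedes randomisation and the adjustment variable is collected afterwards. The comparator includes mental health care and the adjustment holds such care constant. The analysis section has a covariate rule for baseline variables only; the extra rule sits elsewhere, names primary and secondary outcomes, and carries no restriction.

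**Size.** In a linear model the two arm estimates are linked by

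adjusted − unadjusted = −b × (p_MBCT − p_TAU),

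where b is the fitted coefficient for other therapy and p is uptake in each arm (baseline being balanced by randomisation). The shift is zero if uptake is equal. Otherwise its sign depends on b and on which arm has more uptake.

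The article gives no uptake rates and no effects of other therapy, so values were assumed and simulated with 400,000 women per scenario. Uptake followed a logistic model on arm and latent severity; the outcome was linear and adjusted for its baseline score. Only the MBCT effect of 0.5 SD is taken from the document (Sample size). Negative values mean lower symptoms.

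| Scenario | MBCT direct effect | Log-odds of uptake per SD of severity | True effect of other therapy | Uptake MBCT / TAU | Fitted b | Unadjusted | Adjusted | Difference |
|---|---|---|---|---|---|---|---|---|
| A | −0.5 | 1.0 | 0 | 33 % / 33 % | 0.464 | −0.498 | −0.498 | 0.00 |
| B | −0.5 | 1.0 | 0 | 15 % / 33 % | 0.465 | −0.502 | −0.416 | +0.085 |
| C | −0.5 | 0 | −0.5 | 11 % / 30 % | −0.503 | −0.414 | −0.507 | −0.093 |
| D | −0.5 | 1.0 | −0.5 | 15 % / 33 % | −0.034 | −0.411 | −0.418 | −0.006 |
| E | 0 | 1.0 | 0 | 15 % / 33 % | 0.461 | −0.002 | +0.082 | +0.084 |

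The formula agrees with the simulation up to rounding of the uptake rates:

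- B: −0.465 × (0.15 − 0.33) = +0.084
- C: 0.503 × (0.11 − 0.30) = −0.096
- D: 0.034 × (0.15 − 0.33) = −0.006
- E: −0.461 × (0.15 − 0.33) = +0.083

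**Reading the table.** Equal uptake gives no shift (A). Inert therapy taken by sicker women makes the adjusted effect too small (B), and makes MBCT look harmful when it does nothing (E). Effective therapy taken regardless of severity makes it too large for the question asked (C). The two forces can cancel (D). The largest shift, about 0.09 SD, is 0.09 / 0.5 = 18 % of the planned effect.

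**The trigger.** In B the therapy does nothing, yet its coefficient is 0.465. In D it works by 0.5 SD, yet its coefficient is −0.034. An observed association with the outcome does not show whether the therapy had an impact, because sicker women seek it.

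**The case against.** The strongest reply has four parts.

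- **Intention to treat is not violated.** The article defines the term as analysing everyone in the randomised arm, and a covariate does not change that. This stands. A reader might infer that the plan contradicts its own intention-to-treat statement; the text supports only that the rule is unreconciled with the comparison of MBCT plus usual care against usual care.
- **The adjusted model may not be the main one.** The analysis section specifies its models without other therapy, and the reference to later analyses could mean secondary ones. That reading is possible, so it cannot be said that the primary comparison will certainly be adjusted. But nothing in either section confirms it, and the rule names primary outcomes.
- **Uptake may be similar in both arms.** The support-services pamphlet goes to all participants, and the Discussion expects treatment-seeking in both groups. If uptake is equal the shift is nil, so the rule can bias the comparison but need not. A fixed bias towards no effect, which a reader might also infer, is unsupported: scenario C goes the other way.
- **The practical size is modest and the trigger may not fire.** With 26 women per arm, the standard error of an unadjusted difference is about √(2/26) = 0.28 SD, so 0.09 SD is about a third of it. It would be tempting to say that other therapy will nearly always be found associated with outcome; with about 26 per arm and no uptake rates, that cannot be claimed.

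None of this supplies a reason to keep the rule. Whether uptake differs by arm is unknown until the data are in, and the rule does not ask.

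**Conclusion.** The concern holds as a point about an unrestricted, data-triggered adjustment for a post-randomisation variable that belongs to the comparator. The textual part is firm: timing, comparator and missing restriction can all be read in the article. The bias is conditional on uptake differing by arm, and its sign and size cannot be derived from the document. The range of 0 to about 0.09 SD, in either direction, rests wholly on the assumed inputs: uptake of 11 to 33 % with MBCT and 30 to 33 % with usual care, an effect of other therapy between 0 and 0.5 SD, and log-odds of uptake rising by 0 to 1.0 per SD of severity. The open choice of model is a defect whatever the size of the bias.

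**What to change.** Replace the rule under Simultaneous interventions with wording such as:

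> Use of adjunctive mental health treatment will be reported by arm. The main analyses of primary and secondary outcomes will not adjust for it and will use all outcome data regardless of such use. Any analysis accounting for it will be a labelled supplementary analysis with its own estimand and a suitable causal method.

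Align the limitations paragraph of the Discussion, so that it says the data are collected to describe other treatment by arm and to support that supplementary analysis. The worry voiced there, that other treatment may mask a difference between arms, can remain as a stated limitation.

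The cost is wording only. Data collection, visits and sample size are unchanged. The change should be made before outcome data are analysed.
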